### Enrolment

#### Inclusion criteria

All adolescents aged 13-18 years who have had type 1 diabetes for more than one year will be invited to participate together with their parents if they meet the following criteria:

▪ HbA1c ≥ 8.0% at the last visit before entry into the study and

▪ Average HbA1c > 7.5% during the last year before entry into the study.

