### Sample size calculation

The size of the study was based on the primary outcome measure HbA1c. According to a power calculation, an absolute difference of 1.0% in HbA1c between the GSD-Y group and the control group (power 0.8; two-sided level of significance 0.05) could be detected with 26 patients in each group. This calculation was based on a standard deviation of the HbA1c value of 1.3% from a study of coping skills training [45]. To compensate for an attrition rate of 25%, we aimed to recruit 68 patients.

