### Data Collection, Measurements and Analysis Quantitative component

#### Primary outcome

HbA1c will be collected as a routine clinical measurement every third month, which is a standard practice. The capillary blood samples for HbA1c from both hospitals are being analysed at the same department of clinical biochemistry using Variant Analysis Mode, TOSOH Automated Glycohaemoglobin Analyzer HLC-723 G8 (normal range 4.3% - 5.8%).

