### Analysis

To meet Objective 2 and test if GSD-Y effectively reduces HbA1c and improves life skills in adolescents with type 1 diabetes, we will analyse HbA1c and quantitative data from the questionnaires using PAWS Statistics18 for Windows (SPSS Chicago, IL, USA). Statistical analyses will include frequency, mean, standard deviation and confidence intervals. Comparisons of primary and secondary outcomes for the two groups will be conducted comparing data at baseline, at the end of the study, and after a 6-month follow-up period using appropriate parametric tests for variables fulfilling the normal distribution criteria or appropriate non-parametric tests for variables not fulfilling the normal distribution criteria. A Bonferroni correction for multiple testing will be performed.

Improvement of life skills will be defined as increases in HCCQ-scores, TSRQ-scores on autonomy or in relative autonomy index (formed by subtracting TSRQ-scores on control from TSRQ-scores on autonomy), PCD, POPS, WHO-5 and frequency of SMBG per week, and decreases in TSRQ-scores on amotivation, PAID scores and HbA1c. Differences within the GSD-Y group and between the GSD-Y group and the control group will be calculated at the end of the intervention (8-12 months) and after a 6-month follow-up period.

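### The HbA1c comparison gives no stated covariate role to the last-visit value or the prior-year mean, although eligibility already requires both

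*Protocol article*

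**What the plan says.** The Inclusion criteria section of the protocol article sets two joint HbA1c conditions. One concerns the most recent single value, which must exceed or equal 8.0%. The other concerns the preceding twelve months: "Average HbA1c > 7.5% during the last year before entry into the study". Both must be checked before an adolescent can be randomised.

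On measurement, the Primary outcome section under Data Collection says "HbA1c will be collected as a routine clinical measurement every third month, which is a standard practice".

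The Analysis section describes the group comparison as "comparing data at baseline, at the end of the study, and after a 6-month follow-up period". The tests are to be parametric where a variable meets normality criteria and non-parametric where it does not. Baseline appears there as a time point. No covariate is named, and the prior-year average is not mentioned.

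The Sample size calculation section plans for a 1.0% difference at 80% power and two-sided 5%, which it says "could be detected with 26 patients in each group". It uses a "standard deviation of the HbA1c value of 1.3% from a study of coping skills training", with no reduction for any covariate.

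**The concern.** The trial is small: about 26 evaluable adolescents per arm on its own planning figures. At that size, precision is the main limit on what can be said about HbA1c.

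Two pre-randomisation measurements of the outcome variable are in hand for every participant, yet the published comparison gives neither a stated role beyond entry and the baseline time point. If HbA1c levels persist within a person, adjusting for earlier values removes between-person variation from the treatment comparison and narrows its confidence interval. Treatment cannot affect values recorded before randomisation, so adjusting for them is safe.

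The prior-year mean could add to the single baseline value for two reasons. It averages out short-term noise, and the last-visit value is truncated at 8.0% by the entry rule, which weakens it as a predictor.

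**Working it through.** **Inputs from the protocol article.** Difference 1.0%, SD 1.3%, two-sided 5%, power 0.8, 26 per group, 25% attrition, 68 recruited (Sample size calculation). Entry cut-offs: last value at least 8.0%, yearly mean above 7.5% (Inclusion criteria). Three-monthly HbA1c (Primary outcome, Data Collection).

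**Assumptions, not in the article.** Source population mean 8.5% and SD 1.3%. Four quarterly values in the prior year, the last of them serving as baseline. Outcome 10 months after entry. Correlation between HbA1c values 0.5 to 0.8, under three structures.

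**Step 1: reproduce the plan's figure.**
- n per arm = 2(1.960 + 0.842)² × 1.3² / 1.0² = 26.5, rounded up to 27, against 26 stated.
- Standard error at 26 per arm = 1.3 × √(2/26) = 0.361. Noncentrality = 1.0/0.361 = 2.77. Power from the noncentral t with 50 df = 77.6% (79.2% by the normal approximation).
- Attrition: 52/0.75 = 69.3, rounded up to 70, against 68 stated.

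The stated size reproduces closely, without any covariate.

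**Step 2: closed form, ignoring the entry cut-offs, constant correlation 0.6.**
- Residual variance with one prior value: 1 − 0.36 = 0.64.
- With the mean of four: 1 − 4(0.36)/(1 + 3 × 0.6) = 0.486.
- Ratio 0.486/0.64 = 0.76, so 24% less residual variance than with one value.

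**Step 3: apply both entry cut-offs (simulation, 600,000 draws).** Entries are residual variance relative to no adjustment, at assumed correlations 0.5 / 0.6 / 0.7 / 0.8.

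| Structure | Baseline only | Baseline + yearly mean | Extra reduction from the mean |
|---|---|---|---|
| Constant | 0.88 / 0.81 / 0.71 / 0.56 | 0.72 / 0.63 / 0.52 / 0.39 | 18-30% |
| Decaying, ρ·exp(−0.02 × months) | 0.92 / 0.88 / 0.83 / 0.75 | 0.85 / 0.81 / 0.76 / 0.70 | 7-9% |
| AR(1), ρ taken over 10 months | 0.87 / 0.80 / 0.70 / 0.55 | identical | 0% |

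Under AR(1) at 0.6 the yearly mean used alone is a worse predictor than the last value (0.88 against 0.80).

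**Step 4: convert to power and interval width at 0.6.** Residual SD = 1.3 × √ratio, 26 per arm, difference 1.0, noncentral t. Half-width = t(0.975; 50 df) × residual SD × √(2/26).

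| Structure | Power: none / baseline / both | 95% CI half-width (percentage points) |
|---|---|---|
| Constant | 78% / 86% / 93% | 0.72 / 0.65 / 0.57 |
| Decaying | 78% / 82-83% / 86% | 0.72 / 0.68 / 0.65 |
| AR(1) | 78% / 86% / 86% | 0.72 / 0.65 / 0.65 |

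The planning SD of 1.3% is kept throughout so that results compare with the plan. In the simulation the entry rules themselves shrink the outcome SD (to about 1.14 under constant correlation 0.6), so the table shows relative gain and is not a forecast. Charging the extra degrees of freedom lowers power by at most about 0.1 percentage point.

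**The case against.** The strongest reply is that nothing in the article is false or contradictory. The wording on tests is open, a covariate-adjusted model would fit under parametric methods, and covariates are often fixed in an analysis plan, which is not shown here. That stands: the omission cannot be called a decision against adjustment. What remains is that the article describes how the comparison will be made, by a choice of test that turns on normality, and a better-defined method is available from data the trial must already hold.

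Three stronger readings are tempting, and the documents do not support them.

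- A reader might infer that the yearly mean is the best available predictor of the outcome. The article reports no HbA1c correlation or variance component, and under AR(1) the last value predicts better. AR(1) is an extreme, with no measurement noise and no stable personal level, but constant correlation is equally undocumented.
- A reader might infer that the mean supplies precision a single baseline value cannot. The extra gain runs from nothing to 30% of residual variance. Under AR(1) all of the gain, and under decay more than half of the power gain at 0.6, comes from adjusting for baseline alone, which is not specified either.
- A reader might infer a biased or invalid comparison. Randomisation protects the unadjusted contrast, and the stated sample size holds approximately without covariates.

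It is also fair to say that four prior values is an inference. The article calls three-monthly testing standard but does not say how many values form the eligibility average. That average probably includes the last-visit value, so the two covariates overlap.

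**Conclusion.** The point holds as an efficiency improvement. Eligibility requires two pre-randomisation HbA1c measures, and the published comparison gives neither a stated covariate role. On the plan's own 26 per arm, SD 1.3% and difference 1.0%, and an assumed correlation of 0.6, adjusting for baseline lifts power from 78% to about 82-86%, and adding the prior-year mean brings it to about 86-93%. The upper end needs a correlation that does not fall with time. If correlation decays, the mean adds about 3 points of power, and under AR(1) it adds none.

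The first-order gain is baseline adjustment. The prior-year mean is a secondary covariate of uncertain but practically costless benefit. No conclusion of the trial becomes invalid if it is left out.

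**What to change.** In the Analysis section, state that the between-group HbA1c difference at the end of the intervention, and again at 6-month follow-up, is estimated with its 95% confidence interval from a linear model that adjusts for baseline HbA1c, with the prior-year mean used for eligibility as an additional pre-specified covariate. State which measurement counts as baseline.

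Before randomisation, copy the prior-year mean and the number of values behind it from the eligibility check to the case report form.

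The cost is one sentence, one copied data entry and one or two degrees of freedom. No extra blood sample or visit is needed. The number of routine values behind the mean will vary between adolescents, which is why the count should be recorded.

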#### Exclusion criteria

Adolescents will be excluded from participating in the study if they meet any of the following criteria:

▪ Diagnosed with a psychiatric disease

▪ Consulting a psychologist at the time of recruitment

▪ Unable to understand, talk or read Danish.

### Randomisation

Adolescents and parents willing to participate and fulfilling the inclusion criteria will be randomised to either an intervention group (n = 34) (GSD-Y) or a control group (n = 34) (standard care), using stratified randomisation by the adolescent's usual HCP. Randomisation will be performed using sealed envelopes. Neither adolescents nor the HCPs can possibly be blinded to the study. The adolescents in the control group will be offered the GSD-Y intervention after the study has concluded (14-18 month wait-list design).

### Consent

Consent to participate in the study will be obtained by the adolescents' usual HCP. After informed written consent is obtained from the adolescent and at least one parent, adolescents will be randomised into either the intervention or the control group. The adolescent or their parents remain free to withdraw at any time during the study without giving reasons and without prejudicing further treatment. If a participant withdraws consent from further study participation, their data will remain on file and will be included in the final study analysis if the consent for use of the data is not withdrawn; if consent for use of data is also withdrawn, data will be destroyed immediately.

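### HbA1c values collected before withdrawal have no stated route into the between-group comparison, although the Consent section says withdrawn adolescents' data will be included

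*Protocol article*

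**What the plan says.** Three sections of the protocol article bear on this.

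- **Consent.** For an adolescent who withdraws from further participation, "their data will remain on file and will be included in the final study analysis". The only exception is withdrawal of consent to use the data.
- **Primary outcome (Data Collection).** "HbA1c will be collected as a routine clinical measurement every third month, which is a standard practice". So an adolescent has HbA1c values between baseline and the end of the intervention.
- **Analysis.** Groups are compared by "comparing data at baseline, at the end of the study, and after a 6-month follow-up period". The tests are to be parametric or non-parametric, depending on whether a variable is normally distributed; none is named. The next paragraph says that differences "will be calculated at the end of the intervention (8-12 months) and after a 6-month follow-up period".

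The Sample size calculation section adds patients for 25% attrition, and the Randomisation section says that neither adolescents nor providers can be blinded.

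**The concern.** Take an adolescent who withdraws at month 7. Baseline, month-3 and month-6 HbA1c are on file, but there is no end-of-intervention or follow-up value. Of these, the Analysis section gives a place only to the baseline value, which alone says nothing about effect. The inclusion that the Consent section commits to then has no bearing on the main question for this adolescent. The interim values of adolescents who stay are unused too.

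What is at stake is mainly bias. The trial is unblinded and the arms make different demands: one-hour visits with reflection sheets completed beforehand, against standard visits of 30 to 45 minutes. It is plausible, though the article does not say so, that reasons for leaving differ between arms and relate to how HbA1c is going. A comparison limited to adolescents with an end value would then be distorted, while the values that could correct much of the distortion lie unused.

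**Working it through.** **1. How many adolescents could be affected.** Inputs from the Sample size calculation section: difference 1.0%, SD 1.3%, two-sided 5% level, power 0.8, 26 per group, 25% attrition, 68 recruited.

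- n per group = 2 × (1.960 + 0.842)² × 1.3² / 1.0² = 26.5, so 27 (28 by the t-test), against 26 stated.
- Allowing for attrition: 52 / 0.75 = 69.3, so 70, against 68 stated.

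Both agree with the plan to within two patients, and the point does not alter them. The allowance suggests that the sizing counted only adolescents with an outcome value. At 25% attrition, 68 × 0.25 = 17 lack one, leaving 51, or 25.5 per group. Normal-approximation power is 0.784 at 25.5 per group and would be 0.887 if all 34 per group had a value.

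**2. What each value can do under the stated comparisons** (withdrawal at month 7)

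| Value on file | Place in the Analysis section |
|---|---|
| Baseline | Baseline comparison |
| Month 3, month 6 | None stated |
| End of intervention, follow-up | Not observed |

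An adolescent who withdraws after the 8-12 month measurement still counts in the end-of-intervention comparison. The affected group is therefore those without a value at the time point, not all who withdraw.

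**3. Size of the bias under assumed drop-out.** None of the drop-out inputs is in the article. Assumed: 34 per arm; SD 1.3; HbA1c at 0, 3, 6, 9 and 12 months; correlation 0.82 between adjacent values and 0.54 between baseline and month 12; attrition about 25-30%, all before month 12. In the GSD-Y arm, the log-odds of leaving rise by 0.7 to 1.2 per SD of the last HbA1c, so the odds multiply by exp(0.7) = 2.0 to exp(1.2) = 3.3. In the control arm drop-out is random. Results from separately run simulations, no true effect (negative favours GSD-Y):

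| Analysis at month 12 | Bias, percentage points |
|---|---|
| End values, unadjusted | -0.16 to -0.35 across runs (typically about -0.2 to -0.3) |
| End values, baseline-adjusted | -0.06 to -0.15 |
| Change from baseline, those with end values | +0.03 to +0.05 |
| Likelihood analysis of all visits | -0.01 to +0.01 |

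With a true reduction of 1.0, the unadjusted end-value difference averaged 1.15 to 1.27 and the likelihood analysis 0.99 to 1.01. With the same HbA1c-dependent drop-out in both arms and no true effect, all three end-value analyses had bias of about 0.00.

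**4. Plausibility check.** If a fraction d of one arm lacks an end value and their mean would have been D higher than that of the rest, the bias is d × D. For a bias of 0.2 to 0.35, D = 0.2/0.25 to 0.35/0.25 = 0.8 to 1.4 points at d = 0.25, and 0.67 to 1.17 at d = 0.30. GSD-Y leavers would have to be worse than stayers by about that much, with no such pattern among controls.

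**5. Precision when drop-out is unrelated to HbA1c.** In one run the standard error fell from 0.375 to 0.354: 1 - 0.354/0.375 = 5.6%. Across runs the reduction was about 4-6%.

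**The case against.** The strongest reply is that nothing here conflicts. The Consent rule concerns retention and use of data and does not say that every value enters the primary test. It is partly met in any case: baseline data enter the baseline comparison, and case report forms completed at each visit supply pre-withdrawal data on hypoglycaemia, admissions, self-monitoring and attendance. The Analysis section names when differences are calculated, not the only data that may inform them. Missing-data handling is commonly left to a full protocol or analysis plan, which is not shown.

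Much of this stands. A reader might infer that the two sections contradict each other, or that the plan is a completers-only analysis. The documents support neither: no complete-case analysis is named, and imputation, carrying values forward and repeated-measures methods are not ruled out. What remains does not rest on silence. The article makes a commitment about withdrawn data and fixes the comparison time points, and the second as worded gives the interim primary-outcome values no route.

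The bias figures are also fairly challenged. They need HbA1c-driven drop-out in one arm only, and the likelihood analysis is unbiased because drop-out was simulated to depend on observed HbA1c. All attrition is placed before month 12, whereas the article gives 25% without timing in a trial of 14 to 18 months. Using baseline removes more than half of the bias. These limits are accepted in the conclusion.

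**Conclusion.** The point holds as a tension that the Analysis section should resolve. As written, the between-group HbA1c effect rests on adolescents with a value at the time point, and interim values collected before withdrawal do not contribute.

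The size is conditional. With drop-out tied to interim HbA1c in one arm only, at about 25-30% attrition, the bias is roughly 0.2 to 0.35 percentage points unadjusted and 0.06 to 0.15 baseline-adjusted. For scale, the Interventions section cites a 0.4% reduction with the adult version of the method, and the trial is sized for 1.0%. With drop-out unrelated to HbA1c, or working alike in both arms with no true effect, there is essentially no bias. In the unrelated case the gain is the 4-6% smaller standard error, which does not restore the power of a trial without attrition.

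A reader might infer that the trial will overstate the benefit. The documents do not support that: they give no evidence of differential drop-out, and a change-from-baseline analysis was biased slightly the other way. This is a worthwhile improvement using data already collected, not a flaw that invalidates the comparison.

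**What to change.** In the Analysis section, make the primary HbA1c analysis a mixed model for repeated measures on all randomised adolescents whose data may be used. Specify:

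- baseline and every three-monthly HbA1c value up to withdrawal or last visit;
- terms for group, time and group-by-time;
- a rule mapping visits to time points, because the end visit falls anywhere from 8 to 12 months and follow-up from 14 to 18 months;
- the group difference at end of intervention and at follow-up, both taken from this model;
- the comparison of observed end values as a sensitivity analysis.

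This keeps the time points the article already reports and gives the Consent commitment practical effect. The cost is a paragraph of text, the visit-mapping rule and entry of HbA1c values that are measured routinely anyway. The model relies on a missing-at-random assumption, that drop-out is explained by observed values. This should be stated, because it can fail if adolescents leave for reasons the recorded HbA1c does not reflect.

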### Intervention group

The GSD-Y intervention will be delivered by the adolescent's usual HCP in individual settings for a total of 8 visits during an 8- to 12 month period. Each of the 8 visits will last for 1 hour and will include specific reflection sheets, and each visit will cover a specific topic (Table 1). Parents will be invited to participate. However, at least one of the visits can take place without the parents if the involved parties agree. The purpose is to create a safe environment where the adolescents can talk about personal affairs that are confidential and not known by their parents, yet are pertinent to their ability to manage their diabetes (e.g. smoking, drugs, boy/girlfriend). After this type of visit, the adolescents and HCPs will agree on what should be told to the parents, who should tell, and when.

In addition to the visits together with their adolescents, parents will also be offered two visits alone with the adolescents' usual HCPs. The reason for this is to create an environment where the parents can talk about how to act in an autonomy-supportive manner and how to manage their adolescents' shifting readiness to take responsibility for the management of the disease. The first of these parent/HCP visits will be offered after 3 months, and the second will be offered after 6 months. Both of the visits will include specific reflection sheets, and both visits will cover a specific topic (Table 2). After these visits, the parents and HCPs will agree on what should be told to the adolescents, who should tell, and when.

Adolescents will be referred to the dietician if needed. The need for referral will be made by the adolescent, the parents and their HCPs based on the completed reflection sheets from visits 1 and 2. The meeting with the dietician can take place with or without the parents, as decided by the involved parties. Each referral to the dietician involves at least two visits. Each visit is supported by special reflection sheets and covers a specific topic (Table 3).

The adolescents and parents keep their original semi-structured reflection sheets and a copy is put in their file.

### Control group

The control group receives standard care including a number of outpatient visits equal to that of the intervention group: eight visits during an 8 to 12 month period, with a standard duration per visit of 30 to 45 minutes, depending on the hospital.

### Duration

The trial will last from 14 to 18 months for both groups including the 6-month follow-up measurements. The first adolescent began the study in September 2009, and the last adolescent will finish the study in April 2012.

